# A cognitive behavioral therapy intervention to reduce fear of hypoglycemia in young adults with type 1 diabetes (FREE): study protocol for a randomized controlled trial

**DOI:** 10.1186/s13063-019-3876-4

**Published:** 2019-12-30

**Keywords:** Fear of hypoglycemia, Type 1 diabetes, Cognitive behavioral therapy, Randomized controlled trial

## Abstract

**Background:**

In persons with type 1 diabetes (T1D), hypoglycemia is the major limiting factor in achieving optimal glycemic control. All persons with T1D are at risk for hypoglycemia (blood glucose level < 70 mg/dl), which is life-threatening and accompanied by serious physical and psychological symptoms, resulting in profound fear of hypoglycemia (FOH) and reduced quality of life. Young adults with T1D are at risk for FOH and have worse glycemic control and self-management behavior than other age groups with T1D. FOH also results in increased glycemic variability (GV). A major gap exists in how to manage FOH. Our overall objective is to reduce FOH and improve diabetes self-management, glycemic control, and GV in young adults with T1D to reduce or delay diabetes complications and improve quality of life. We aim to (1) determine the feasibility and acceptability of an eight-week cognitive behavioral therapy (CBT)-based Fear Reduction Efficacy Evaluation (FREE) intervention in young adults with T1D who experience FOH; and (2) determine the impact of the FREE intervention, compared to an attention control group, on the outcomes FOH, self-management, glycemic control (A1C), and glycemic variability (continuous glucose monitoring recordings).

**Methods/design:**

A randomized controlled trial in 50 young adults aged 18 to 35 years with T1D will be used. Eligible subjects will be randomized to the intervention program (Fear Reduction Efficacy Evaluation [FREE]) or attention control group. A one-week run-in phase is planned, with baseline measures of FOH, self-management behavior, A1C, and real-time continuous glucose monitoring recordings (RT-CGM) to calculate GV for both groups. The intervention group will participate in eight weekly individual one-hour sessions using CBT and exposure treatment for specific fears. RT-CGM and a daily FOH diary will be used as feedback cues as part of the FREE program. The attention control group will participate in eight weekly individual one-hour diabetes self-management education (DSME) sessions and wear a RT-CGM device (to measure GV only) over 8 weeks. At completion, FOH will be measured, and RT-CGM recordings will be analyzed to determine differences between the FREE and control groups.

**Discussion:**

Findings from this proposed pilot study will serve as the foundation for a larger trial to reduce FOH and improve self-management, glycemic control, and GV.

**Trial registration:**

ClinicalTrials.gov: A cognitive behavioral therapy (CBT) intervention to reduce fear of hypoglycemia in type 1 diabetes, NCT03549104. Registered June 7, 2018

## Background

In persons with type 1 diabetes (T1D), iatrogenic hypoglycemia is the major limiting factor in achieving optimal blood glucose control [1]. All persons with T1D are at risk for hypoglycemia (blood glucose level < 70 mg/dl [2]), which is life-threatening [3] and has serious physical and psychological sequelae. One psychological sequela is fear of hypoglycemia (FOH) [4, 5]. FOH can be incapacitating, causing panic [4], anxiety [6], phobic disorders [7], and greatly diminished quality of life (QOL) [8].

Despite advances in insulin therapy and glucose-sensing technology, FOH remains a critical deterrent to T1D self-management, psychological well-being, and QOL [9]. Fear is conceptualized as an emotion arising from a cognitive appraisal of a specific threat or danger [10]. Normal fear is adaptive, stimulating more vigilance and improved performance; heightened fear leads to increased anxiety and may result in a delay to action or inappropriate action [10–12]. Fear may mimic the symptoms of hypoglycemia and impair its detection, exacerbating the problem [5, 13]. At the extreme, fears can develop into anxiety disorders and phobias [7, 11, 14].

Previous negative experiences of hypoglycemia influence diabetes self-management behaviors [9, 15–20]. Diabetes self-management is defined as the knowledge, skills, and behaviors needed for diabetes self-care [21]. Insulin doses may be inappropriately reduced and diet may be modified to avoid hypoglycemia. Dietary modifications may include excessive eating, particularly more carbohydrates [22, 23] or snacking at night [19, 24]. These modifications lead to increased glycemic variability (GV; the intra-day fluctuations in blood glucose) and poor glycemic control. Registry data from the T1D Exchange Clinic Registry revealed that only 13% of young adults achieved glycemic targets [25], and, in a survey of self-management practices, 45% of young adults reported that they did not reach their glycemic goals due to FOH [9].

Young adulthood is the developmental period from age 18 to 35 years, when individuals transition to independent diabetes care, as well as establish independence, careers, family, and parenthood [26]. This is before the onset of long-term diabetes complications, when healthy behavior changes can have a critical impact on future health [27].

Over the past three decades, newer technologies have been designed to help patients with diabetes manage their treatment regimens, including continuous glucose monitoring (CGM) systems, insulin pumps, sensor-augmented pump therapy with insulin suspend features, and insulin bolus calculators. While these have improved glucose control (i.e., A1C), improved A1C has not consistently translated into reduced FOH [28–34]. Diabetes education programs typically discuss FOH but have limited strategies to manage it [4]. Glucose management and blood glucose awareness training have had variable effects on FOH [4, 35–43]. Outcomes demonstrated that, as glucose levels lower, worry levels do not consistently decrease [43]. We hypothesize that the lack of consistent and sustainable reductions in FOH has occurred because the focus of these programs has been on glycemic control, not FOH.

GV has been associated with more frequent episodes of hypoglycemia [44] and fluctuations between glucose extremes (i.e., hypo- to hyperglycemic), which may occur with overtreatment of a hypoglycemic episode. Evidence supports the role that GV plays in generation of oxidative stress [45], endothelial dysfunction [46], and diabetes complications in T1D [47]. GV has also been associated with increased risk for cardiovascular events [63]. Though A1C provides a biomarker for average blood glucose over a 2- to 3-month period, it does not capture daily blood glucose fluctuations (Fig. 1). Individuals may have an optimal A1C yet high GV [48]. GV is influenced by self-management behavior [49] and amenable to change with appropriate intervention.

**Fig. 1 Fig1:**
[figure not shown]
Glycemic variability

The proposed study will pilot test a cognitive behavioral therapy (CBT)-based program to decrease FOH and examine its association with GV. Heightened fear develops from memories of previous negative hypoglycemic events that create a conditioned negative response to future fear triggers [11, 50]. The conditioned fear response is reframed through cognitive restructuring of negative thoughts, regulation of emotions (FOH), and changing maladaptive behaviors (self-management behavior). Exposure therapy will be used to reduce FOH that is out of proportion to the threat through habituation to previously fearful situations (Fig. 2) [51]. Real-time continuous glucose monitor (RT-CGM) readings and fear diary review will be feedback cues to reinforce learning. The goal is not to replace standard diabetes therapy, but improve diabetes self-management [52] through reducing fear. The CBT intervention will be compared to usual diabetes education currently in place to address self-management behavior.

**Fig. 2 Fig2:**
[figure not shown]
Cognitive-behavioral model of FREE

The specific aims for this study are:

In 50 young adults with T1D (18–35 years) [26] who experience FOH, we will:
Determine the feasibility and acceptability of an eight-week CBT-based Fear Reduction Efficacy Evaluation (FREE) interventionDetermine the impact of the FREE intervention, compared to an attention control group, on the outcomes FOH, self-management, glycemic control (A1C), and glycemic variability (RT-CGM recordings)

Primary hypothesis: Young adults with T1D participating in the FREE program will demonstrate improvement in FOH compared to the attention control group.

Secondary hypothesis: Young adults with T1D participating in the FREE program will have improved self-management, glycemic control, and glycemic variability (GV) compared to the attention control group.

## Methods/design

A randomized controlled design using parallel groups will be used to test the study hypotheses. Institutional Review Board approval was obtained (April, 2018) prior to initiating the study from the University of Illinois Office of the Protection of Human Subjects.

### Study population and recruitment

Eligible participants will include young adults (18–35 years) with T1D ≥ 1 year, receiving care from an endocrinologist, experiencing FOH (screening questionnaire) [53], who have previously attended a basic diabetes educational program. Exclusion criteria are pregnancy or breastfeeding, receiving psychotherapy for FOH, and having a co-existing chronic illness or receiving medications (excluding insulin) that may influence diabetes self-management or GV.

Participants will be recruited through two medical centers and local diabetes organizations and websites in the midwestern United States. Informed consent will be obtained from each study participant by a trained member of the study team. Those who meet study criteria will be scheduled for an appointment for the start of the one-week run-in period (week 0) and apply a RT-CGM device with instructions on its care. Participants will be randomly assigned to the FREE intervention or attention control group. During the study period, participants will continue to receive their usual diabetes care, and their health care providers will continue to care for their diabetes as they normally would.

Participants will be assigned a unique code number. A master list that links the subject identity to the data will be kept by the principal investigator (PI) and stored in a locked office separately from the data. All data will be stored and analyzed by code number. The coded data will be entered into a password-protected computer with a secure server for analysis. Paper copy data will be stored in a locked office.

Criteria for discontinuing participation for a given trial participant include: a) participant request or b) determination by the psychologist/interventionist that continuation of the study would not be appropriate due to confounding psychological issues that become evident during the study. If this occurs, a list of counseling resources will be provided.

### Sample size determination

The sample size estimate will allow examination of within-group and between-group differences from beginning to end of the intervention and to calculate effect sizes to power a future larger study. To determine the sample size to meet these goals, the mean, SD, and mean/SD of FOH levels from our pilot studies were used to estimate the expected effect size [48]. The expected estimated effect size was 0.72. Twenty-five subjects will be required in each group (treatment and control; *n* = 50 total). A 20% attrition rate is expected, based on previous psychoeducational interventions in T1D [39, 41, 43]. Thus, we will accrue 30 subjects per group, to achieve a final sample size of 25 subjects per group (*n* = 50 total).

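### The planning effect size of 0.72 is not traced to a FREE-versus-control difference, 30 accrued per arm leaves 24 rather than 25, and the pilot's own effect size is to power the larger trial

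*Protocol article*

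**What the plan says.** All the sizing text is in the protocol article, Methods/design, Sample size determination.

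- **Purpose.** "The sample size estimate will allow examination of within-group and between-group differences from beginning to end of the intervention", and also "to calculate effect sizes to power a future larger study".
- **Source of the effect size.** "the mean, SD, and mean/SD of FOH levels from our pilot studies were used to estimate the expected effect size".
- **Effect size and number required.** "The expected estimated effect size was 0.72. Twenty-five subjects will be required in each group". Attrition of 20% is expected, so 30 per group are to be accrued, with 25 per group stated as the final number.

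The primary hypothesis, at the end of the Background, is a between-arm contrast: FREE participants "will demonstrate improvement in FOH compared to the attention control group". The Statistical analysis section plans a repeated-measures mixed-effects model. Table 3 schedules the FOH scale at weeks 0, 4, 8 and 12. The article gives no alpha, target power, sidedness or test for the sample size.

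**The concern.** Three stated elements do not fit together well.

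1. A standardised between-arm effect is the difference between two arms divided by an SD. The mean and SD of FOH levels give the SD, but they do not give the difference. The section names no treatment-versus-control contrast, and the Background says the programme is being pilot tested in this trial.
2. The number accrued does not deliver the stated number of completers at the stated attrition.
3. The effect size that this pilot observes is meant to power the larger study, but about 24 per arm estimates it very imprecisely.

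At stake is how the result is read and used. Anyone who takes 25 per arm as the size required for the primary comparison may read more into a null result than it supports. A larger trial sized on this pilot's estimate could be several times too small or too large.

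**Working it through.** **Inputs.** From the article: d = 0.72, 25 completers per arm, 30 accrued per arm, 20% attrition, equal groups. Assumed, because the article does not give them: alpha 5% (10% also tried), one- or two-sided, power 70% or 80%, and a range of baseline/follow-up correlations r.

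**1. Can 25 per arm be reproduced?** The normal approximation is n = 2(z_α + z_β)²/d², with d² = 0.5184. Exact answers use the noncentral t.

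- Two-sided 5%, 80% power: 2 × (1.960 + 0.842)²/0.5184 = 30.3, so 31. Noncentral t: 31.3, so 32.
- One-sided 5%, 80% power: 2 × (1.645 + 0.842)²/0.5184 = 23.9, so 24. Noncentral t: 24.6, so **25**.
- Two-sided 10%, 80% power: noncentral t 24.6, so **25**.
- Two-sided 5%, 70% power: noncentral t 24.8, so **25**.

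Several standard settings return 25. Two-sided 5% with 80% power and no adjustment does not.

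**2. Attrition.** 25 × 1.2 = 30 reproduces the accrual figure. But 30 × (1 − 0.20) = 24 completers. Keeping 25 would need 25/0.80 = 31.25, so 32 accrued per arm.

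**3. Power of the between-arm comparison at d = 0.72, unadjusted t-test.**

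| Completers per arm | Two-sided 5% | One-sided 5% | Effect detectable with 80% power, two-sided 5% |
|---|---|---|---|
| 25 | 70.3% | 80.6% | 0.81 SD |
| 24 | 68.5% | 79.2% | 0.83 SD |

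**4. Credit for the baseline measurement.** If 0.72 is on the raw-score SD, adjusting for baseline with correlation r multiplies that SD by √(1 − r²). The effective effect is then 0.72/√(1 − r²).

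- With 25 per arm, 80% power at two-sided 5% needs an effective effect of 0.809. So √(1 − r²) = 0.72/0.809 = 0.890, which gives r of about 0.45 to 0.46.
- With 24 per arm it needs 0.826. So √(1 − r²) = 0.72/0.826 = 0.872, which gives r of about 0.49.
- At r = 0.5 the effective effect is 0.72/0.866 = 0.831. Power is about 82% with 25 per arm and about 80.5% with 24.
- At r = 0.4 it is 0.72/0.917 = 0.786. Power is about 78% with 25 per arm and 76% with 24.

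**5. Precision of the pilot's own estimate.** Suppose it observes exactly 0.72 with 24 per arm, unadjusted. Then t = 0.72 × √(24/2) = 2.494 on 46 degrees of freedom. The exact 95% limits of the noncentrality parameter, divided by √12, give 0.13 to 1.30. At two-sided 5% and 80% power, the next trial would need 905 per arm at the lower limit, 32 at the point estimate and 11 at the upper limit.

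**The case against.** The strongest reply is that nothing here is a demonstrated miscalculation. The article is a condensed account, and alpha, power and sidedness may stand in the full protocol. The hypotheses are worded directionally, and one-sided 5% with 80% power gives exactly 25. The planned analysis is a repeated-measures model, so an unadjusted t-test understates its power at any non-zero correlation. The section also serves within-group comparisons, and if 0.72 is a within-group effect, a paired two-sided 5% test with 25 has 93% power. This is a pilot, and estimating effect sizes is an accepted pilot aim.

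Most of this stands, and it rules out three stronger readings that a reader might infer:

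- **That 25 is an arithmetic error, or can come only from a one-sided test.** The article fixes no test settings, and step 1 shows more than one route to 25.
- **That 0.72 simply is the mean/SD of FOH scores.** The text lists mean, SD and mean/SD as ingredients and does not say how they were combined. The pilot figures are not in the document, so the derivation cannot be checked.
- **That the larger trial will rest on the point estimate alone.** The article says effect sizes will be calculated to power it, but not that nothing else will be used.

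The reply leaves other parts untouched. No between-arm difference is named as the source of 0.72, and no choice of alpha or sidedness supplies one. Directional wording of a hypothesis does not declare a one-sided test. The within-group power does not address the primary hypothesis. The 24 follows from the section's own figures.

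**Conclusion.** The point holds as one of justification and reporting. For the between-arm primary hypothesis, 0.72 SD is a planning assumption, because its stated source is FOH levels and no FREE-versus-control contrast is named. The expected number of completers is 24 per arm, one short of the stated 25. The shortfall is small in itself, but it should be stated correctly.

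On an unadjusted two-sided 5% test, power for 0.72 SD is about 68% with 24 per arm, against about 70% with 25. It reaches 80% with 24 only if baseline adjustment is used and the correlation is about 0.49 or more. That rests on an assumed correlation and on 0.72 being expressed in raw-score SDs. A bare statement that the trial has 68% power would therefore also mislead.

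Using the pilot's effect size to power the larger study is a weak method whatever the sidedness: the interval of 0.13 to 1.30 spans required sizes from 905 down to 11 per arm. Baseline adjustment would narrow that interval (by a factor of about 0.87 at r = 0.5), which still leaves it wide.

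**What to change.** Keep enrolment at 30 per arm and change the wording of Sample size determination.

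1. Replace the statement of the requirement with text such as: *With 30 accrued per arm and 20% attrition, about 24 completers per arm are expected. A between-arm difference of 0.72 SD in the HFS-II worry score is a planning assumption. At two-sided 5%, unadjusted power is about 68% for 0.72 SD and 80% for 0.83 SD. Baseline adjustment raises this, for example to just over 80% for 0.72 SD if the baseline/follow-up correlation is 0.5.* If the team did intend a one-sided test, the text should say so and give the matching figure (about 79% with 24 per arm).
2. Say which contrast and which SD 0.72 refers to, and how the earlier pilot figures led to it.
3. Replace the aim of calculating effect sizes to power the larger trial with text such as: *The between-arm estimate will be reported with its 95% CI. The larger trial will be sized on a minimally important difference in the HFS-II worry score, using this pilot's SD, baseline/follow-up correlation and retention.*

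The cost is in wording, with no extra participants. The stated figures will look less favourable, and the team must justify a minimally important difference.

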### Randomization and masking

Randomization will be computer-generated (using REDCap) with permuted blocks in multiples of two and stratified by gender. The randomization process will be overseen by the study statistician (CP). The treatment allocation will be concealed until the time of randomization. Due to the nature of the intervention, participants and their respective interventionists will be aware of their treatment allocation. The project manager will also be aware of the treatment allocation; all other study staff will be masked. Study participants will enter questionnaire data for the primary study outcome directly into REDCap. Secondary outcomes are objectively measured, and those who will analyze these outcomes will be masked to treatment allocation until study completion. At the baseline visit, the project manager and study participant will be informed of the treatment allocation through REDCap. The project manager will then coordinate the first intervention visit with the appropriate interventionist. If an adverse event occurs, unmasking would be permissible.

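### At the stated 20% attrition, 30 per group leaves an expected 24 per group (48 in total), not the stated 25 (50): a minor slip in the attrition adjustment

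*Protocol article*

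**What the plan says.** The section on sample size determination in the protocol article gives three linked figures. The requirement is "Twenty-five subjects will be required in each group", 50 in total. The loss allowance is "A 20% attrition rate is expected, based on previous psychoeducational interventions in T1D". The conclusion, presented as following from these two, is "we will accrue 30 subjects per group, to achieve a final sample size of 25 subjects per group". No other section gives a different attrition rate or accrual target.

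Elsewhere the article gives only the final size. The methods part of the abstract describes "A randomized controlled trial in 50 young adults aged 18 to 35 years", and the specific aims at the end of the Background begin "In 50 young adults with T1D".

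The same section reports an expected effect size of 0.72. It states no significance level, sidedness or power.

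**The concern.** The accrual target is offered as the number that delivers 25 per group once 20% have left. If 20% do leave, it does not. The plan then falls short of its own requirement on its own assumption, without any bad luck.

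The form of the error also matters a little beyond this trial. The study is a pilot whose stated purposes include supplying effect sizes to power a larger trial, and retention is one of its feasibility outcomes. The same adjustment carried forward at 20% attrition would leave the larger trial 4% below its target (1.2 x 0.8 = 0.96).

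A secondary point is that the abstract and aims call this a trial in 50 people, although the plan is to accrue 60.

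**Working it through.** **Inputs**, all from the section on sample size determination:
- required final size: n = 25 per group, 50 in total
- attrition: d = 0.20
- planned accrual: 30 per group, so 2 x 30 = 60 in total

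**1. Reproducing the plan's figure.** n x (1 + d) = 25 x 1.20 = 30. This matches exactly, so the allowance appears to have been added as 20% of the final number. Attrition is a fraction of those enrolled, not of those who remain.

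**2. Forward check.** 30 x (1 - 0.20) = 24 per group, and 60 x 0.80 = 48 in total. The shortfall is 1 per group and 2 overall.

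**3. Attrition at which 30 would leave 25.** 1 - 25/30 = 16.7%.

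**4. Accrual that meets 25 at 20% attrition.** n/(1 - d) = 25/0.80 = 31.25, so 32 per group and 64 in total. Check: 32 x 0.80 = 25.6. Rounding does not explain the plan's figure, because 31.25 rounds to 31 or 32, not to 30.

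**5. Effect on precision.** For an analysis of completers only, the standard error of a between-group difference scales with the square root of 1/n. The ratio is sqrt(25/24) = 1.021, about 2% wider.

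**6. Effect on power (illustrative).** The article states no alpha, sidedness or power. With an assumed alpha of 0.05, the stated effect size of 0.72 read as a standardised between-group difference, and a two-sample t-test:

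| Test | 25 per group | 24 per group |
|---|---|---|
| Two-sided | 70.3% | 68.5% |
| One-sided | 80.6% | 79.2% |

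The loss is between 1 and 2 percentage points.

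**7. Chance of keeping at least 25.** This assumes that each participant completes independently with probability 0.80.

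| Accrued per group | One group keeps at least 25 | Both groups do |
|---|---|---|
| 30 | 43% | 18% |
| 32 | 70% | 49% |

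The two rows must be read together. Even the correctly inflated target misses about half the time in at least one group, so much of the risk at 30 is ordinary chance variation and not the arithmetic error.

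**The case against.** The best defence is that the gap hardly matters. It is one participant per group in a pilot that claims no power, and estimating effect sizes for a later trial does not turn on 24 against 25. The planned analysis is also an intent-to-treat mixed-effects model with repeated measures, and Table 3 schedules the fear of hypoglycemia scale at weeks 0, 4, 8 and 12. Someone who leaves after week 4 can still contribute data, so 24 completers is not necessarily the analysis sample. All of this stands, and it is why the point is minor. It does not make the three stated figures agree.

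A reader might go further in two ways that the document does not support.

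- **That the plan overstates its power or precision.** The article reports no power and no interval width, so there is no stated figure to correct.
- **That the plan has two competing trial sizes, leaving it unclear whether accrual stops at 60 enrolled or at 50 completers.** The sample size section itself links the two numbers: 60 are accrued in order to leave 50. Nothing in the article suggests stopping at 50 completers. The abstract and aims quote the intended final size. That is loose wording, not a contradiction about when accrual ends.

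**Conclusion.** The point holds as a minor arithmetic error. On the article's own figures, 30 per group at 20% attrition leaves an expected 24 per group (48 in total), and 25 per group would need 32 accrued (64 in total). This rests on nothing outside the sample size section.

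The power comparison and the retention probabilities rest on the assumptions named with them and serve only to show scale. On that scale the practical consequence is slight, and it does not threaten the pilot's aims. It is worth correcting because a stated sample size is wrong and restating it costs almost nothing.

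**What to change.** In the section on sample size determination, keep 30 per group (60 randomised) and restate the expected final size as about 24 per group (48 in total) at 20% attrition. Say openly that this is one per group below the stated 25, and that 32 per group (64 in total) would be needed to meet it.

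As a conforming edit, have the abstract and the specific aims give 60 randomised, with about 48 expected to complete, in place of the bare 50.

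The cost is wording only. Accrual does not change, and the stated final size becomes slightly less favourable.
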